**Fig. 2 Fig2:**
[figure not shown]
Overview of the study process. Figure Legend – * Participants will not be informed about the randomisation process until the end of the study

### Sample size

The number of mother-infant pairs required was calculated using the conventional formula [24] for two sample t-test:
*N* = 16*(SD^2^/D^2^) (N = number per group, SD = standard deviation, D = Difference between group).

The SD and D were obtained from the results of the MOM study [10], which assessed the effects of relaxation meditation tape on reducing maternal stress assessed by PSS between intervention and control groups (D = 3.13, SD = 5.00). A sample of 82 mother-infant pairs (41 per randomised group) would allow the detection of a 3.13 points difference in perceived stress between groups at 80% power with a significance level of 0.05. Considering the microbiome analysis in the present study will only be conducted in vaginal delivered mothers, which account for approximately 40% of the total sample, a larger sample is required. However, the effect size in the present study may be larger than the MOM study, as mothers with preterm infants are likely to be more stressed than mothers with healthy term infants, which were examined in the MOM study. Thus, a total of 120 infants will be recruited.

### Randomisation and blinding

The baseline assessment will be conducted during the one week postpartum home visit. After recording the demographic characteristics of mothers and their early feeding experience, participants will be randomly assigned to either intervention arm or control conditions (standard management) by randomisation envelope. A member of the research team who will have no contact with participants will produce the randomisation schedule using a computer random number generator, and prepare the assignments in sealed opaque envelopes. Randomisation will be stratified by gestational age (34–35 weeks, 36–37 weeks), delivery mode (vaginal, caesarean), and by the study centre (four community clinics). Participants will not know about the randomisation until the end of the study; they will be aware that the aim of the study is to investigate factors that may make breastfeeding easier for mothers with an LPI or ETI, so they can breast-feed for longer. The researchers will be blinded during the data analysis process; however, they cannot be blinded during data collection since additional materials (diary for recording the use of relaxation tape) will be collected during the data collection period.

### Data collection

Measures of maternal stress, anxiety, infant behaviour and appetite will be recorded at each home visit; participants can choose to fill the questionnaires on paper or online in their own time after the visit. A breast milk sample will be collected pre-feed and infant anthropometry will be assessed by a trained nurse pre-feed at each home visit. Feed duration will be noted by the trained nurse. Details about the data collection in each visit are shown in Fig. 3.

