**Method:**

A single blind parallel randomised controlled trial will be conducted in Chinese primiparous mothers who deliver a infant (34 0/7–37 6/7) weeks and plan to exclusively breastfeed. Mothers will be recruited from four local community clinics attached to Beijing Children Hospital. Two home visits will be arranged at one week and eight weeks postpartum. Participants will be randomly assigned to either intervention arm or control (no intervention) before the first home visit. Mothers from the intervention group will be asked to listen to an audio recording with relaxation meditation daily during breastfeeding. Maternal stress and anxiety will be measured at one week and eight week postpartum using Chinese version of Cohen’s Perceived Stress Scale (PSS) and Beck Anxiety Inventory (BAI). Infant weight and length gain (as SD scores) from one to eight week will be measured using anthropometry. Milk volume will be measured using 48-h test-weighing method. Breast milk samples and mother and infant’s stool samples will be collected to measure macronutrient and microbiome content. Anthropometric measurements (weight, length and head circumference) will be performed during all home visits.

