### Hypotheses and outcome measures

#### Primary hypotheses

The use of a relaxation therapy by breastfeeding mothers of LPI and ETI that will be given from one week to eight week postpartum, will result in:
reduced maternal stress and anxietygreater infant growth, specifically increased weight and length gain

Primary outcomes and measures
maternal stress and anxiety at one week and eight week postpartum, measured by Chinese version of Cohen’s Perceived Stress Scale (PSS) and Beck Anxiety Inventory (BAI) respectively.infant weight and length gain (as SD scores) from 1- to 8-week measured using anthropometry.

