### Study population and recruitment

The study population will be recruited from four local community clinics located in different districts of Beijing. The target sample population is Chinese primiparous mothers with a singleton pregnancy who are breastfeeding their LPI or ETI. Eligible mothers (Table 1) will be approached 2–3 days after delivery when they stay at the hospital and breastfeeding is successfully established. The information sheet will be provided to mothers who are interested. A research assistant will explain the outline of the study but will not mention the randomisation. Mothers will be asked to read through the information sheet carefully and discuss with their family.

**Table 1 Tab1:** Eligibility criteria for mother and infant

Inclusion criteria	
Chinese primiparous mothers	
Singleton pregnancy	
Free from any disease that will influence breastfeeding	
Non-smoker	

After discharge from the hospital, the parents will be contacted by the local clinic to see if they are interested in taking part and the first home visit for baseline assessment will be scheduled at the one-week postpartum follow-up. Eligible participants will be asked to sign the consent form. All questionnaires and the information sheets are in Chinese. An overview of this study is provided in Fig. 2.

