### Statistical analysis plan

All questionnaires and anthropometric data will be analysed using IBM SPSS (version 24). Intention-to-treat analysis will be performed for comparing primary outcomes (perceived stress and anxiety, infant weight and length gain from baseline to the endpoint) between intervention and control groups at the eight week postpartum using two sample t-test. Paired t-test will be used to compare baseline to post-intervention changes of each primary outcome. The association between the effects of the intervention and the frequency of use will be examined by two-tailed Pearson correlation. Two-sample t-test will be used to compare the changes in milk volume, energy and macronutrients level between intervention and control group. Regression analysis will be used to adjust for confounding factors.

Furthermore, associations between infant temperament/behaviour and the composition of microbiota in mother’s breastmilk, mother and infants’ gut will be examined using univariate ANOVA. Multiple regression analysis and MANOVA will be used to detect differences among significant predictor variables identified by ANOVA.

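### The protocol gives two times for randomisation and lets one-week stress and anxiety forms be completed after the visit, so baseline PSS and BAI may follow allocation and tape use

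*Protocol article*

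**What the plan says.** **When mothers are randomised.** The Abstract (Method) states: "Participants will be randomly assigned to either intervention arm or control (no intervention) before the first home visit". Randomisation and blinding states that "The baseline assessment will be conducted during the one week postpartum home visit" and continues: "After recording the demographic characteristics of mothers and their early feeding experience, participants will be randomly assigned". Study design says only that assignment follows written consent.

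**When the questionnaires are completed.** Data collection has stress, anxiety, infant behaviour and appetite recorded at each home visit, but adds that "participants can choose to fill the questionnaires on paper or online in their own time after the visit". It makes no exception for the first visit and sets no time limit. Table 2 lists PSS, BAI, BEBQ, IIFAS and the three-day behaviour diary at one week.

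**When the intervention starts.** Under Primary hypotheses the therapy is one "that will be given from one week to eight week postpartum". The section on the recording asks for use as often as possible, ideally daily. It gives no handover date.

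**How the one-week values are used.** The primary measures include "maternal stress and anxiety at one week and eight week postpartum". The Statistical analysis plan section compares PSS and BAI between arms at eight weeks by two-sample t-test. It also plans paired tests of change from baseline for each primary outcome, a correlation between intervention effect and frequency of use, and regression adjustment for confounders that it does not name.

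**The concern.** The two statements on when randomisation happens cannot both be followed. Under either one, the protocol leaves room for the one-week PSS and BAI to be completed after the arm is known to the team, and after an intervention mother has begun listening.

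A score taken after treatment has begun is not a baseline. If the tape lowers stress early, the intervention arm's one-week mean is already reduced, and anything that subtracts or adjusts for it removes part of the effect. In a change-based correlation with frequency of use, the heaviest early users would tend to have the most lowered baselines, which weakens the association. A table of baseline characteristics would mix pre- and post-treatment values. Analysis cannot recover a true baseline afterwards, and the article does not mention recording when each form was completed.

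**Working it through.** **1. The order of events, side by side**

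| Step | Abstract | Methods |
|---|---|---|
| Randomisation | before the first home visit | at the one-week visit, after demographics and early feeding experience |
| One-week PSS, BAI | at one week, so after randomisation | at the visit or later in the mother's own time |
| Tape use | daily during breastfeeding, start not dated | from one week; handover not dated |

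The Methods name demographics and feeding experience as coming before the envelope. They do not say that nothing else does, but neither do they place PSS or BAI there. Handover at the first visit is inferred from the one-week start. Figures 2 and 3, which may show the order, are not available here.

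**2. The plan's own figure**

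The Sample size section gives D = 3.13, SD = 5.00 and N = 16 × SD²/D² per group.

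16 × 25.00 / 9.7969 = 40.83, rounded up to 41 per group, 82 in total. This reproduces the stated figure and is not in dispute. It rests on a between-group difference, not on change.

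**3. What a late baseline would do**

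The documents give neither of these inputs, so both are assumptions:

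- f = share of the 3.13-point effect already present in the intervention arm's mean one-week PSS. It combines how many mothers complete the form late with how quickly the tape acts.
- r = correlation between one-week and eight-week PSS. With equal SDs at both times, it is also the regression slope.

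Formulas:

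- Unadjusted eight-week difference: 3.13, whatever f is.
- Points lost from the intervention arm's paired change: 3.13 × f.
- Between-arm difference in change: 3.13 × (1 − f).
- Baseline-adjusted difference: 3.13 × (1 − r × f).

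| f | Lost from paired change | Difference in change | Adjusted, r = 0.3 | Adjusted, r = 0.5 | Adjusted, r = 0.7 |
|---|---|---|---|---|---|
| 0 | 0 | 3.13 | 3.13 | 3.13 | 3.13 |
| 0.10 | 0.31 | 2.82 | 3.04 | 2.97 | 2.91 |
| 0.25 | 0.78 | 2.35 | 2.90 | 2.74 | 2.58 |
| 0.50 | 1.565 | 1.565 | 2.66 | 2.35 | 2.03 |

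For example, at f = 0.25 and r = 0.5: 3.13 × 0.75 = 2.35, and 3.13 × (1 − 0.125) = 2.74.

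**4. Power of the unaffected comparison**

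With 120 recruited and equal arms (60 each), the unadjusted eight-week comparison of a 3.13-point difference has 92.9% power by the normal approximation, before any attrition. A late baseline does not change this.

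**The case against.** The strongest reply is that the main comparison of stress and anxiety does not use the baseline at all. It is a two-sample t-test at eight weeks. The phrase about gain from baseline belongs most naturally to infant weight and length, which a nurse measures at the visit. The paired tests are within-arm and do not estimate the treatment effect. The protocol states a between-arm comparison of change for the milk measures ("Two-sample t-test will be used to compare the changes in milk volume, energy and macronutrients level between intervention and control group"), not for PSS or BAI. All of this stands, and it limits the point to the analyses that use the one-week questionnaires.

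Own-time completion is also only an option: many mothers may fill in the forms at the visit, before the envelope is opened. That stands too, so contamination is possible, not certain. Mothers' ignorance of the randomisation limits expectation effects, but not the effect of listening to the tape.

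Two stronger readings are tempting:

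- *Mothers are randomised before they consent.* A reader might infer this from the Abstract's order together with the consent step in Study population and recruitment ("Eligible participants will be asked to sign the consent form"). Study design explicitly puts randomisation after written consent, and the recruitment section does not fix consent to the visit itself. The documents do not support a planned breach.
- *A one-week milk-volume weighing would also follow allocation.* The Discussion describes supplying the scale ahead of the eight-week collection, and no visible text schedules a one-week weighing. This is conjecture.

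**Conclusion.** The concern holds in a limited form. The Abstract and the Methods contradict each other on when randomisation happens. The own-time clause allows one-week PSS, BAI and the other questionnaires to be completed after allocation and, if the tape is handed over at the first visit, after its use has begun.

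The analyses at risk are the paired tests of PSS and BAI, any change-based correlation with frequency of use, any regression that adjusts for one-week PSS or BAI, and baseline comparability. If the tape lowers stress early, the bias is towards no effect, so it is unlikely to create a false positive. The questionnaire clause does not bias the unadjusted eight-week PSS and BAI comparison or nurse-measured infant growth.

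The size cannot be derived from the documents. The table is an illustration under assumed f and r. A reader might infer that a large part of the planned 3.13-point effect will be lost. That would need an unsupported value of f, applied to a between-arm PSS change analysis that the protocol does not clearly plan.

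This should be fixed because the remedy is cheap and a lost baseline cannot be recovered, but it does not undermine the main comparison of stress and anxiety.

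**What to change.** - Align the Abstract with Study design and with Randomisation and blinding.
- State one order for the first visit: consent; one-week PSS, BAI, BEBQ and IIFAS, at the visit or online beforehand; envelope opened; tape handed over.
- In Data collection, remove the after-the-visit option for the one-week questionnaires. Leave the eight-week forms as the Discussion describes them: given out a week ahead and returned at the vaccination contact.
- Record the date and time of each questionnaire and of opening the envelope.
- The one-week behaviour diary covers 72 hours and may run past allocation. Compare infant behaviour between arms at eight weeks, as the secondary outcome already names, and not as change from week one.

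The cost is protocol wording, a visit checklist, and a few more minutes at the first visit or online before it. No extra participants are needed.

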**Fig. 3 Fig3:**
[figure not shown]
Home visit during the data collection. Figure Legend – *BAI* Beck Anxiety Inventory, *BEBQ* Baby Eating Behaviour Questionnaire, *IIFAS* Iowa Infant Feeding Attitude Scale, *PSS* Perceived Stress Scale

### Intervention tool: the relaxation therapy recording

The tape used in this study is based on a meditation CD designed for breastfeeding mother [25]. The recording was transcribed and translated into Chinese language by a certified yoga therapist. A brief version of the recording was tested and compared with other four relaxation techniques in a pilot study [26] and was demonstrated to be the most effective approach for breastfeeding mothers to relax. Mothers in the intervention group will be given the tape and will be asked to listen to the recording as frequently as possible while breastfeeding or expressing milk, preferably at least once a day. Mothers will be asked to record their use of the tape in a diary book.

### Questionnaires

Questionnaires that will be used in this study are outlined in Table 2. All questionnaires are available in Chinese. The Chinese version of PSS, BAI, BEBQ, and IIFAS have been used among postnatal women in previous studies, which have presented reasonable validity and reliability.

**Table 2 Tab2:** Questionnaires for the BABY study

Questionnaire	Time point for the use of questionnaires			
	First visit 1 week	Final visit 8 week	3 month follow-up	6 month follow-up
Demographic questionnaire	✓			
Perceived stress scale	✓	✓		
Beck Anxiety Inventory	✓	✓		
Baby Eating Behaviour Questionnaire	✓	✓	✓	✓
Iowa Infant Feeding Attitudes Scale	✓	✓	✓	✓
3 day Infant Behaviour Diary	✓	✓		

#### Cohen’s perceived stress scale (PSS)

PSS is a psychological self-rating scale for measuring the perception of stress on a scale of five, from 0 (never) to 4 (very often). The original 14-item English version of PSS was developed by Cohen and his colleagues. As a global measure of perceived stress, it appears to be reliable and validated for the measurement of stress in chronic conditions. The present study will use the 10-item Chinese version of PSS, which has been validated for the Chinese population (Cronbach’s α = 0.85–0.86) [27, 28].

#### Beck anxiety inventory (BAI)

BAI is a 21-question multiple-choice self-reported inventory that consist of 21-items that is used to measure the severity of anxiety from different aspect on a scale of four, from 0 (not at all) to 3 (severe). Research demonstrated that the BAI have high internal consistency and reliability (Cronbach’s α = 0.94). The present study will use the translated Chinese version of BAI, which has been validated for the Chinese population (Cronbach’s α = 0.74–0.87) [29, 30].

#### Baby eating behaviour questionnaire (BEBQ)

BEBQ is derived from an existing psychometric measure validated for older ages, the Children’s Eating Behaviour Questionnaire, supplemented by a review of the literature on milk-feeding behaviours. It has been used in a large birth cohort study in the UK (*n* = 4804), and appears to be reliable with Cronbach’s alpha values ranging from 0.73 to 0.81 [22]. BEBQ can be used to measure infant appetite and eating behaviour during the period of exclusive milk feeding, which makes it well-suited for the neonates. It consists of 18 items designed to measure four traits: “enjoyment of food” (4 items), “food responsiveness” (5 items), “slowness in eating” (4 items), and satiety responsiveness” (5 items). The mothers in this study will be asked to rate all items based on a scale from 1 (never) to 5 (always).

#### The Iowa infant feeding attitude scale (IIFAS)

The questionnaire is designed to measure maternal attitudes toward infant feeding methods. It consists of 17 questions and the mother will be asked to give their opinion based on a scale from 1 (strongly disagree) to 5 (strongly agree). This questionnaire has been used extensively and has been tested for reliability with Cronbach’s alpha ranging from 0.62 to 0.74 [31, 32].

#### 3-day infant behaviour diary

Infant crying behaviour will be recorded at one and eight weeks home visit using a validated three day diary. The diary consists of a time scale for 72 h, which is divided into 15 min segments, and has five categories of behaviour: Sleeping, Awake and content, Fussy, Crying and Feeding [33, 34].

### Other assessments

#### Anthropological measurements on mothers and infants

Mothers and infants will be weighed at the one week and eight week home visit. The weight will be measured to the nearest 0.1 kg using an electronic scale. Anthropometric measures on the infants also include recumbent length and head circumference. Each measure will be repeated three times and the mean value will be used. All measurements will be done following the detailed instructions provided by the World Health Organization instructions on child assessment.

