#### Test-weighing

For the measurement of milk intake, researchers will lend a digital electronic infant weight scale to mother for 48 h and mother will be asked to weigh her infant right before and right after a feeding, and the duration between the two weight measurements will be recorded to adjust for insensible water loss. Care will be taken to ensure that the infant is weighed with the same clothing before and after the feed. The difference in weight, adjusted for insensible water loss during the feeding period, is the amount of breastmilk the infant consumed during the feeding.

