## Discussion

One of the strengths of our study is that it has been designed to minimize disruption for the participants since the data collection points have been timed to coincide where possible with routine clinic visits and home visits. According to the health policy in China, the maternity leave is 98 days. During this time, the majority of mothers will practice a traditional postpartum confinement at home and keep routine contact with the community clinic where they are registered. In Beijing, most community clinics will schedule a routine home visit at one week postpartum for all registered mothers. Hence, the baseline assessment of this study is scheduled at one week postpartum when the trained clinic nurses conduct their routine home visit. Thus our baseline assessment and data collection can be conducted during their routine home visit to reduce imposing an extra interruption and additional burden on the mother. Moreover, since there is a routine contact, the nurse can provide the scale and the eight week questionnaires during the contact one week prior to the eight week data collection. Mothers can fill in the questionnaires using their leisure times and return the scale and questionnaires when they take their infant to the clinic for the second month vaccination; the nurse can also conduct the eight week sample collection and infant anthropometry measurement during the time when mothers bring their infants to the clinic for vaccination. These routine contacts with local clinics should help to reduce the potential attrition rate.

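### Infant weight, which feeds a primary outcome, is recorded only to the nearest 0.1 kg: a small, unbiased and avoidable loss of precision that triplicate readings only partly offset

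*Protocol article*

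**What the plan says.** Under Anthropological measurements on mothers and infants, the protocol article states: "Mothers and infants will be weighed at the one week and eight week home visit". The next sentence gives the resolution: "The weight will be measured to the nearest 0.1 kg using an electronic scale". No separate figure for infants appears there or elsewhere. The same paragraph adds "Each measure will be repeated three times and the mean value will be used" and refers to an external standard: "All measurements will be done following the detailed instructions provided by the World Health Organization instructions on child assessment".

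The primary outcomes include "infant weight and length gain (as SD scores) from 1- to 8-week measured using anthropometry". The Statistical analysis plan section compares "infant weight and length gain from baseline to the endpoint" between arms by two-sample t-test.

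A second infant weighing procedure appears under Test-weighing: "researchers will lend a digital electronic infant weight scale to mother for 48 h". Its purpose is to measure the milk taken at single feeds. The resolution of that scale is not given.

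**The concern.** A 0.1 kg step is ordinary for an adult and coarse for an infant in the first two months. The primary outcome is a difference between two such weights, so rounding enters twice. Because the resolution sentence directly follows one that names both mothers and infants, it reads as a specification for infants too, not as a detail left open.

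What is at stake is precision on a primary endpoint. The sample size was derived from perceived stress alone, and the article states no power for weight gain, so there is no stated margin to absorb avoidable measurement error. The milk-intake procedure, which serves a secondary outcome, presumably needs finer weighing than the primary outcome is given.

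**Working it through.** **The plan's own figure.** The only computed design figure is the sample size for perceived stress: 16 × 5.00² / 3.13² = 40.8, so 41 per group and 82 in total. It reproduces. It does not depend on weight resolution, so neither 82 nor the target of 120 changes.

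**Inputs from the article.** Recording step w = 0.1 kg; two weighings (weeks 1 and 8); three readings averaged; outcome is gain as an SD score; total recruitment 120.

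**Assumptions (not in the article).**
- Weight SD of 0.4 to 0.5 kg at week 1 and 0.5 to 0.7 kg at week 8.
- SD of the SD-score gain of 0.5 to 1.0.
- Rounding errors uniform and independent at the two visits, which is reasonable when weights spread over many 0.1 kg steps.

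**Rounding error in kg.**
- Per weight: w/√12 = 0.1/3.464 = 0.029 kg.
- For the gain: 0.029 × √2 = 0.041 kg.
- Worst case for one infant: 0.05 + 0.05 = 0.1 kg.

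**Effect of three readings.** If the three agree, they round to the same value and the mean keeps the full 0.029 kg. Simulating the mean of three rounded readings with noise between readings gives:

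| Noise SD per reading (kg) | Error SD, mean of 3, rounded (kg) | Error SD, mean of 3, unrounded (kg) |
|---|---|---|
| 0 | 0.029 | 0 |
| 0.005 | 0.026 | 0.003 |
| 0.01 | 0.024 | 0.006 |
| 0.02 | 0.022 | 0.012 |
| 0.03 | 0.024 | 0.017 |

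Averaging helps somewhat, but the error stays above what unrounded readings would give. Mean bias was about zero in every row.

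**Rounding error in SD-score gain**, taking the full 0.029 kg: √[(0.0289/SD₁)² + (0.0289/SD₈)²].
- SDs 0.4 and 0.5 kg: √(0.00521 + 0.00333) = 0.092.
- SDs 0.45 and 0.6 kg: 0.080.
- SDs 0.5 and 0.7 kg: √(0.00333 + 0.00170) = 0.071.

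**Variance and power.** Extra variance is (error SD / SD of gain)². The power of a comparison planned at 80% becomes Φ(2.802/√(1 + extra) − 1.960).

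| Error SD | SD of SD-score gain | Extra variance | Power |
|---|---|---|---|
| 0.092 | 0.5 | 3.4% | 78.7% |
| 0.080 | 0.7 | 1.3% | 79.5% |
| 0.071 | 1.0 | 0.5% | 79.8% |

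In participants this is 120 × 0.005 = 0.6 to 120 × 0.034 = 4.1, so roughly 1 to 4 of 120.

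**Cross-check in kg.** With an SD of the gain of 0.3 to 0.6 kg, extra variance is (0.041/0.3)² = 1.9% down to (0.041/0.6)² = 0.5%, and power is 79.3% to 79.8%. At 0.2 kg the figures are 4.2% and 78.4%.

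**With a 10 g step.** The error SD falls to 0.003 kg per weight and 0.004 kg for the gain. The extra variance falls a hundredfold, to at most 0.034% in the table above.

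**The case against.** The strongest reply is that the effect is negligible: a few percent of variance at most, under SDs the article does not supply, with no bias and no change to any stated design figure. That stands, and it sets the weight of the point. It does not remove it, because a better specification costs almost nothing.

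A second reply is that the 0.1 kg was meant for mothers, or that the cited WHO instructions set a finer step for infants. Either may be so. The text does not say the first, and the content of the instructions is not in the article, so an explicit figure cannot be taken as overridden. The remedy would be the same in both cases.

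A reader might also infer more than the article supports:

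- **That the repeats are useless.** This is true only if the readings agree. With noise of 5 to 30 g between readings, the error SD drops from 0.029 to between 0.022 and 0.026 kg.
- **That the trial already has a finer scale at both weighings, so the fix is free.** Measuring single feeds makes a finer scale likely, but its resolution is not stated. The Discussion describes the loan only around week 8, with mothers to "return the scale and questionnaires when they take their infant to the clinic for the second month vaccination". The planned comparison of changes in milk volume hints at a baseline measurement, but nothing shows that scale in use at the week 1 weighing.
- **That the two weights come from different scales with an offset between them.** The article places the eight-week infant measurement both at home and at the clinic, but it identifies the scale at neither and gives no basis for sizing an offset. The conflict over place needs reconciling in its own right; it does not add to the rounding problem.

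**Conclusion.** The point holds as a minor one. The only stated resolution is 0.1 kg, it applies on its face to infants, and it feeds a primary outcome. The rounding error of 0.029 kg per weight and 0.041 kg for the gain follows from the recording step when repeat readings agree. The cost of about 0.5% to 3.4% in variance of SD-score gain, and of at most about 1 to 2 points of power, rests on assumed SDs.

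It would be wrong to conclude that the weight outcome is invalid or biased. Rounding acts alike in both arms and averages to about zero, so it widens the confidence interval slightly and does not shift the estimate.

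**What to change.** Split the resolution sentence in Anthropological measurements on mothers and infants: mothers to the nearest 0.1 kg; infants to the nearest 10 g or finer on an infant scale, with the same scale or scale model at week 1 and week 8. State the resolution of the test-weighing scale, and whether it is available at week 1, if it is to serve for this.

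The cost is a wording change, a line in the nurse instructions, and ensuring that a suitable infant scale is at hand at both weighings. No visit or procedure is added.

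As a separate correction, reconcile the place of the eight-week infant measurement. The Abstract, Data collection and Anthropological measurements sections put it at a home visit; the Discussion allows it at the clinic vaccination contact.
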